### Outcome measures

The effectiveness of intervention will be evaluated on a range of caregiver and child outcomes. The outcome measures will be administered by the trained assessment team blind to the allocation status of participants at baseline (at the time of recruitment, ie, third trimester of pregnancy), 6 and 12 months’ postpartum. The self-report outcome measures will be orally administered by the trained assessment team blind to the allocation status of the participants. The detail of the outcome measures is given below (see table 2 for schedule of assessments).

**Table 2 T2:** Schedule of assessments

S. no.	Outcomes		Time points		
		Screening	Baseline third trimester of pregnancy	6 months postpartum	12 months postpartum
*Primary outcome*					
1.	OMCI				X
*Secondary outcomes*					
2.	SRQ	X	X	X	X
3.	WHO-QoL		X		X
4.	MSPSS		X		X
5.	WHODAS		X		X
6.	Maternal empowerment-brief questionnaire		X		X
7.	BSID-III				X
8.	ASQ3				X
9.	Home inventory				X
10.	Weight and height measurements				X
11.	Early breastfeeding-brief questionnaire			X	
12.	Diarrhoeal episodes-brief questionnaire			X	X
13.	Immunisation-record form			X	X
14.	CSRI				X

ASQ3, Ages and Stages Questionnaire-3; BSID-III, Bayley Scale of Infant Development-III; CSRI, Client Service Receipt Inventory; MSPSS, Multidimensional Scale of Perceived Social Support; OMCI, Observation of Mother–Child Interaction; SRQ, Self-reporting Questionnaire; WHODAS, WHO Disability Assessment Schedule; WHO-QoL, WHO, Quality of Life.

#### Primary outcome

Caregivers–child interaction: maternal responsive caregiving behaviours will be assessed at 12 months’ postpartum across two-arms (primary endpoint) using the OMCI tool.^22^ OMCI tool is based on responsive parenting framework proposed by Landry and colleagues.^23^ The tool comprises of 19 items related to maternal and child behaviours. Maternal behaviours include maternal affect, maternal touch, maternal verbalisation, sensitivity and contingent responses, scaffolding, language stimulation and focus; whereas, child outcomes include, child affect, child focus, child’s communication efforts and mutual enjoyment. The scoring is done by recording the frequency of the occurrence of each of the above-mentioned behaviours during the mother–child interaction. The sum is calculated by adding the scores of mother and child domains; where higher score indicates more responsive interactions. The tool has been designed to live rate mother–child interaction of 2 years old toddlers in low resource settings of rural Pakistan. It has been extensively used in similar population in Pakistan and found to be sensitive to detect change in mother–child interaction as a result of receiving responsive caregivers intervention at 12 and 24 months postpartum.^22^ In the present study, the research assistants will observe a live 5 min mother–infant interaction while mother and infant will play together with a picture book.

### Infant secondary outcomes

*Bayley’s Scales of Infant Development (BSID III)*^24^ will be used to measure cognitive, language, motor, socioemotional development and adaptive behaviour at 12 months’ postpartum. The tool has been used previously in similar South Asian settings.^25 26^*Ages and Stages Questionnaire 3rd Edition (ASQ3)***27** will be used to measure developmental delays in communication, gross motor, fine motor, problem solving and personal social domains at 12 months’ postpartum. It provides cut-off score in five domains of development that indicates possible need for further evaluation. It highlights results that fall in a ‘monitoring zone’, to make it easier to keep track of children at-risk. The tool has been validated to use in South Asian community settings.^26 28^Home environment measured by *Home inventory:*^29^ quality and quantity of stimulation and support in the child’s home will be measured using home inventory at 12 months’ postpartum. The tool has been validated to use in Pakistan.^30^*Anthropometric measurements:***31** infants in both groups will be weighed and measured with standard techniques at 12 months’ postpartum. Growth data will be converted into SDs (Z scores) for weight and length with WHO Anthro (V.3.2.2).*Early breastfeeding (EBF)*:**32** assessors will document what the infant was fed in the last 24 hours at 6 months postpartum. This information will be categorised as either EBF, partial breastfeeding (giving an infant some breastfeeding, and some additional foods, either milk, cereal or other food items) or no breastfeeding. If the infant will not exclusively breastfeed, details of when (age of infant) and why EBF was discontinued will be recorded. At the first 6 months follow-up, details about early initiation, discarding colostrum, use of prelacteals and reasons for delaying or not initiating breastfeeding will be assessed.The number of *diarrhoeal episodes* in the infants during the 2 weeks before interview will be recorded at 6 and 12 months’ postpartum, with a questionnaire used in previous studies.^33^ Diarrhoea will be defined as three or more unformed stools passed in 24 hours, and a diarrhoeal episode will be defined as being separated from another episode by at least three diarrhoea-free days.Records of *immunisation* will be assessed for all infants in the study, and infants will be classified as those with or without up-to-date immunisation status 6 and 12 months’ postpartum.

### Maternal secondary outcomes

Maternal distress will be measured by the *SRQ*^34^ at baseline, 6 and 12 months postpartum. SRQ is a 20-item self-report measure to detect non-specific psychological distress, developed by the WHO. Psychological distress is represented by subscales of depression/anxiety, somatic symptoms, reduced vital energy and depressive thoughts. The SRQ items are scored 0 or 1. A score of 1 indicates the presence of symptoms of psychological distress during past month and a score of 0 indicates the absence of symptoms. The maximum score indicates the presence of higher psychological distress. A score of >9 indicates increased risk of maternal distress/postpartum depression.^8 35^Caregivers’ health-related quality of life will be measured by *WHO Quality of Life (WHOQoL)-Brief version* at baseline and 12 months postpartum. WHOQoL assess the participants position in life in the context of the culture and value systems in which they live and in relation to their goals, expectations, standards and concerns. WHOQoL comprises of four domains namely physical health, psychological health, social relationships and environment. Items are rated on a 5-point Likert scale, where 1 represents ‘disagree’ or ‘not at all’ and 5 represents ‘completely agree’ or ‘extremely’.The level of social support will be measured using *Multidimensional Scale of Perceived Social Support (MSPSS)***36** will be measured baseline and 12 months’ postpartum. It includes 12 items which cover three dimensions: support from family, friends and significant other. Each item is rated on a 7-point Likert-scale (1=*very strongly disagree*; 7=*very strongly agree*). A total score is calculated by summing the responses of all items (range 12–84) with higher scores indicating higher levels of perceived social support.Caregiver’s level of functioning will be measured using *WHO Disability Assessment Schedule (WHODAS)***37** at baseline and 12 months’ postpartum. WHODAS assesses participants’ health-related difficulties in the level of functioning in six domains of life (understanding and communicating; moving and getting around; attending to one’s hygiene, dressing, eating and staying alone; interacting with other people; domestic responsibilities, leisure, work and school and joining in community activities, participating in society) over the past 30 days.*Maternal financial empowerment*: women’s empowerment will be measured at baseline and 12 months postpartum, using a questionnaire consisting of: (a) two items previously used in the same population^38^ that assess financial empowerment (ie, whether a woman is given a lump-sum of money for day-to-day expenses and whether she can make independent decisions about its use). Women who answer ‘yes’ to both items on financial empowerment will be classified as ‘empowered’.Utilisation of healthcare will be measured by CSRI adapted for perinatal population of Pakistan, at 12 months postpartum.^32^

As the study is being conducted amidst COVID-19, all in-person assessments will be conducted by following appropriate precautionary measures.

### Randomisation and blinding

The participants were randomised into intervention or control arm on a 1:1 basis using computerised software by an independent researcher. The allocation concealment was ensured by keeping random sequence in sequentially numbered, opaque, sealed envelopes, at the off-site centre. Only assessment team (conducting baseline and follow-up assessment) will be blind to the treatment allocation of trial participants. To maintain the blinding, all trial participants will be briefed, prior to the assessment about the significance of blinding and the importance of not disclosing their allocation status to the assessment team members. If unblinding does occur, this will be documented, the assessment will be halted and a new assessor will be assigned to complete the assessment.

### Safety measures

In the present study, a referral pathway, based on the existing referral system, has been established to ensure the safety of the study participants. The IoP is the tertiary mental healthcare facility in the north of Pakistan and situated within the public tertiary healthcare facility and teaching hospital, the Benazir Bhutto Hospital, Rawalpindi. It caters to the mental health needs of the populations in the metropolitan city of Rawalpindi and is the specialist referral facility for common mental health problems identified at the adjacent primary healthcare centres. In our study, if a participant discloses any event of abuse, intimate partner violence or is at imminent risk of harm to herself and others, identified at the time of assessment or during the intervention delivery, the research team will record the event and referral to the IoP will be made for appropriate medical, medico-legal and psychosocial assessment and rehabilitation by a multidisciplinary team led by qualified psychiatrists.

### Adverse events reporting

All adverse events (AEs) and serious AEs reported by the trial participants, their husband and in-laws of recruited participants, LHWs or observed by the investigator or the research team (assessment and intervention team) will be recorded by data manager. AE is defined as any undesirable experience occurring to a subject during the time frame of the study, whether or not considered relevant to the research procedure. All AEs will be collected by assessment team at 12 months’ postpartum follows and will be reviewed periodically by trial steering committee (TSC) which will determine the necessary steps to be taken with respect to the ongoing trial.

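### Adverse events are actively collected only at 12 months postpartum, yet reviewed periodically; facilitators add an earlier reporting source in the intervention arm alone, so a pooled comparison risks ascertainment bias

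*Protocol article*

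**What the plan says.** All references are to the protocol article.

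- **Definition (Adverse events reporting).** An AE is "any undesirable experience occurring to a subject during the time frame of the study", so the reference period is the whole of each woman's participation.
- **Sources (same section).** AEs and serious AEs are recorded when "reported by the trial participants, their husband and in-laws of recruited participants, LHWs or observed by the investigator". The list ends with "the research team (assessment and intervention team) will be recorded by data manager".
- **Collection and review (same section).** "All AEs will be collected by assessment team at 12 months’ postpartum follows and will be reviewed periodically by trial steering committee". On the review in full, these events "will be reviewed periodically by trial steering committee (TSC) which will determine the necessary steps to be taken with respect to the ongoing trial".
- **Assessment visits (Outcome measures; Table 2).** The blinded team sees every woman at baseline, that is "third trimester of pregnancy), 6 and 12 months’ postpartum". AE collection is tied to the last of these visits only.
- **Contacts by arm.** The abstract gives 15 facilitator sessions in the intervention arm (Table 1 has 19 rows). The control arm has no facilitator. Under Treatment as-usual, the number of LHW visits is the same whatever the allocation.
- **Blinding (Randomisation and blinding).** Only the assessment team is blind.
- **Committee (Ethics).** The trial steering committee (TSC) meets monthly, and intervention staff are among its members.

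**The concern.** Two features of the AE section do not fit their purpose.

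The first is timing. A committee that meets monthly and may act on the running trial needs AE information as it arises. The one enquiry that puts the same question to every woman in both arms comes at the end of her follow-up. Staggered enrolment means that some 12-month reports arrive while other women are still being followed, but each of those reports looks back over more than a year.

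The second is evenness. Until the 12-month visit the record is built from unsolicited reports, and one source of these, the facilitators, is in regular contact with intervention mothers only and knows the allocation. The Safety measures section has the same shape: abuse, violence or imminent risk of harm is recorded when found at an assessment (both arms) or during intervention delivery (one arm).

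At stake are the committee's ability to judge safety during the trial and the fairness of any later AE table by arm. The primary outcome is not affected.

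**Working it through.** **1. Length of the look-back.** Inputs: enrolment at 28 gestational weeks (Inclusion criteria) and the enquiry at 12 months postpartum. Birth at 40 weeks is assumed.

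- To the 12-month visit: (40 − 28) + 52 = 64 weeks.
- With a 6-month enquiry (26 weeks) added: the first look-back is 12 + 26 = 38 weeks and the second is 26 weeks.

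**2. Women who may never be asked.** The sample size section allows for 20% attrition: 0.20 × 125 = 25 per arm. A woman lost before 12 months misses the only scheduled AE enquiry. A 6-month enquiry would reach those lost after that visit.

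**3. Sources available before 12 months.**

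| Source | Intervention | Control |
|---|---|---|
| Participant, husband, in-laws | yes | yes |
| LHWs (equal number of visits) | yes | yes |
| Assessor, chance observation | yes | yes |
| Assessor, scheduled AE enquiry | no | no |
| Facilitator (unblinded) | yes | no |

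The record before 12 months is two-sided, with one additional source in one arm.

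**4. The plan's own figure.** The AE section states no number. The arm size used below comes from the sample size section and reproduces: a two-sided t-test with effect size 0.4, 80% power and alpha 0.05 needs 99.08, rounded up to 100 per arm; 100 / 0.8 = 125 per arm, 250 in total, as stated.

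**5. Illustration of pooling.** The document gives no AE rate and no capture rate, so everything here is assumed. Let p be the true risk, equal in both arms; s the proportion of affected women picked up through sources common to both arms, including the 12-month enquiry; and f the proportion of the remainder picked up by facilitators.

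- Recorded risk, control: p × s.
- Recorded risk, intervention: p × [s + (1 − s) × f].
- Recorded risk ratio: 1 + (1 − s) × f / s. The true risk cancels.

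With p = 0.20, s = 0.6, f = 0.5:

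- Control: 0.20 × 0.6 = 0.12, or 15.0 of 125.
- Intervention: 0.20 × (0.6 + 0.4 × 0.5) = 0.16, or 20.0 of 125.
- Risk ratio: 0.16 / 0.12 = 1.33. A two-sided 5% test of these proportions would reject about 15% of the time.

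Risk ratio over the assumed range:

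| s | f = 0.2 | f = 0.5 | f = 0.8 |
|---|---|---|---|
| 0.4 | 1.30 | 1.75 | 2.20 |
| 0.6 | 1.13 | 1.33 | 1.53 |
| 0.8 | 1.05 | 1.12 to 1.13 (1.125) | 1.20 |

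For true risks of 10% to 30%, the rejection rate under no true difference runs from about 5% to 83%. With f = 0, or with the comparison confined to a collection that is the same in both arms, the ratio is 1.00 and the rejection rate 5%. The direction is always toward more recorded AEs in the intervention arm.

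**The case against.** The case on the other side has several parts.

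- **AE recording is not confined to 12 months.** A reader might infer that nothing is recorded earlier. The text does not support that. Events observed by the research team, which includes the assessors, are recorded without a visit limit, and the Safety measures section covers any assessment. What is missing at 6 months is a scheduled enquiry. This stands, and the point is limited to scheduled collection.
- **The control arm is not invisible.** Participants, relatives and LHWs can report in both arms throughout. LHWs visit new mothers monthly, with equal visit numbers by arm. One cannot say that control-arm events surface mainly by recall at 12 months, or that the committee sees one arm only. This also stands: the shared sources reduce the imbalance, but they do not remove it.
- **No between-arm AE comparison is described.** The Statistical analysis section leaves detail to a statistical analysis plan that is not shown. A reader might infer that the AE comparison is biased, but that cannot be asserted: one confined to the blinded 12-month collection would be even-handed. What remains is that the AE section sends all sources to one record and states no rule for separating them.
- **The wording is garbled.** The reference to 12-month follows could be meant to cover follow-ups during the 12 months. The preposition points to a single visit, but the reading is not certain. If several visits were meant, the text should say so.
- **AEs are peripheral here.** The intervention is psychosocial, and AEs are neither in the outcome schedule (Table 2) nor in the sample size. This limits the weight of the point. It does not reconcile the collection schedule with a periodic review that can alter the trial.

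**Conclusion.** The point holds in a limited form. As written, the one scheduled, blinded AE enquiry comes at 12 months postpartum, about 64 weeks after enrolment if enrolment is at 28 weeks and birth at term. It cannot supply a periodic review with even-handed data for women who have not yet reached that visit. Before then the committee works from unsolicited reports, with facilitators as an extra, unblinded source in the intervention arm.

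Any AE summary that pools all sources is at risk of ascertainment bias toward more events in the intervention arm. The size is not derivable from the document. The ratios of 1.05 to 2.20 rest entirely on assumed capture rates (40% to 80% for the shared sources, 20% to 80% of the remainder for facilitators), and better shared capture would bring the ratio closer to 1.00. They show direction and sensitivity and are not an estimate for this trial. The change is worth making because it is cheap and uses a visit that already takes place.

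**What to change.** Amend the Adverse events reporting section as follows.

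1. Elicit AEs and SAEs with the same checklist in both arms at the existing 6-month and 12-month blinded assessments, and pass the 6-month data to the TSC's periodic review.
2. Record the source of each AE.
3. Base the main between-arm AE summary on the solicited AEs. Also report by arm the deaths and SAEs that reach the trial through channels common to both arms, so that events in women lost before a visit are not dropped. A comparison confined strictly to visit-elicited events would leave these out, and the plan itself allows for 20% attrition.
4. List events known only through facilitators separately. They remain visible to the committee.

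The cost is a few extra minutes at the 6-month visit, a source field in the AE record and a sentence or two on the safety summary. No referral or treatment rule needs to change.

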### Data management

The baseline and follow-up assessments data will be collected by the assessment team on android-based application using hand held devices (tablets). Data will be stored at the secure web server and will be checked for consistency and quality at the end of each day. All data sets will be stored in password-protected computer, only accessible by the responsible individual. The data collected in hard copies (collected by the interviewers) will be safely stored in locked cabinets. Qualitative data will be fully anonymised and coded. No identifying names or details will be recorded.

### Statistical analysis

The findings will be reported according to the Consolidated Standards of Reporting Trials guidelines for randomised controlled trial^39^ (figure 1). This will include the flow of research participants through each stage of the trial, including the number eligible, randomly assigned, receiving the intended treatment, completing the study protocol and analysed for the primary outcome. The primary analyses will be on intent-to-treat basis consisting of all participants included according to the arms in which they are randomised and secondary analyses will be based on per-protocol population.

For the analysis of the primary outcome (caregiver–child interaction across two-arms at 12 months postpartum), a linear regression model will be employed with treatment as the sole predictor. In addition, adjusted linear model analysis will be performed with the prespecified covariates (gender of infant, mother’s education and severity of mothers’ psychosocial distress measured using SRQ) measured at baseline being added into the above linear model. The crude and adjusted mean differences in the primary outcome together with its 95% CIs at 12 months will be derived from the linear models. In addition, subgroup analysis of primary endpoint will be performed on the above prespecified covariates.

Analysis of secondary continuous outcomes with single follow-up measurement will be done in a similar fashion as the primary endpoint analysis. Analysis of secondary continuous outcomes with repeated follow-up measurement will be performed using a linear mixed model with treatment visit, interaction between treatment and visit as fixed effects, the baseline value of the outcome as covariate, if it is available and subject as random effects. The analysis of binary outcomes will also use a generalised linear/mixed model depending on whether there will be a repeated measurement. ORs with their 95% CIs will be derived from the generalised linear/mixed model analysis. Missing primary outcome and secondary outcomes with a single measurement will not be imputed; whereas, missing secondary outcomes with repeated measurements will be imputed in sensitivity analysis using the last observation carried forward strategy. Missing baseline covariates will be imputed using simple imputation methods in the covariate adjusted analysis based on the covariate distributions in the sample. For a continuous variable, missing values will be imputed from random values from a normal distribution with mean and SD calculated from the available sample. For a categorical variable, missing values will be imputed from random values from a uniform distribution with probabilities *P*_1_, *P*_2_, … and *P*_k_ from the sample. Seed for the imputation will be set as the date of data analysis. The study is powered to make a single comparison in the primary outcome at 12 months only. All analyses will be described in detail in the statistical analysis plan. SAS V.9.4 and SPSS V.21 will be employed for the statistical analyses.

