## Methods and analysis

### Study design

A two-arm, single-blinded, individual randomised controlled trial with mixed-methods process monitoring and evaluation is being carried out to evaluate the effectiveness of intervention. The participants are recruited from a rural subdistrict, randomised into intervention and control arms, on a 1:1 allocation ratio.

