### Sample size calculations

The power calculations are based on one primary outcome, that is, mother–child interaction on OMCI tool^22^ at 12 months’ postpartum. The scoring of tool is based on the frequency of the occurrence of responsive behaviours of mother with higher scores indicating more responsive interactions. The effect size for the present study was estimated based on the findings of a similar study conducted in Pakistan, where OMCI was used as one of the outcomes to evaluate the effect of responsive stimulation intervention on caregiver–child interaction at 12 and 24 months postpartum.^8^ The findings of the study showed mother–child dyads receiving responsive caregiving intervention had significantly higher mean scores on OMCI at 12 months (mean 32.3 (SD: 8.3) vs mean 27.1 (SD: 8.2), p<0.0001) than those who were allocated to control arm. Moreover, repeated-measures analysis showed that effects were sustained at 24 months. As the effect sizes for OMCI in Yousafzai *et al* 2015’s study ranged between 0.6 and 0.9; therefore, a conservative effect size of 0.4 (two-sides hypothesis) at 12 months post-partum was proposed in the present study. The effect size was calculated using the two-sided t-test. Assuming an effect size of 0.4, with 80% power, 0.05 significance and a two-sided hypothesis test and accounting for 20% attrition, we will need 250 caregiver–child dyads (125 in each arm).

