### Training and supervision of non-specialist facilitators in ‘Nurturing Care’ intervention

The delivery agents of the ‘Nurturing Care’ intervention are female non-specialist facilitators who are graduates in psychology/social sciences with little or no prior experience of delivering psychosocial interventions to mothers with perinatal distress and their new-born infants and have achieved competency to deliver ‘Nurturing Care’ intervention following training and practice sessions. These non-specialist facilitators were selected from the universities in the study subdistrict through a job advertisement and interviews.

A cascade model of training and supervision has been followed to deliver ‘Nurturing Care’ intervention. The training consisted of classroom teaching of basic theoretical concepts of ‘Nurturing Care’ intervention, its strategies, group discussions and role-plays. The programme trainers trained 15 non-specialist facilitators. The training consisted of 10-days class-room training followed by practice cases under the supervision of programme trainer. The participants of this practice group were pregnant women without distress and their infants, selected from the same community after seeking informed consent for participation in the training. The programme trainer performed live competency rating during practice cases using an adapted version of ENhancing Assessment of Common Therapeutic (ENACT) factors tool for ‘Nurturing Care’ intervention (Kohrt *et al* 2015). Only competent non-specialist facilitators (mean score above 2.5 on all domains of adapted ENACT) have been allowed to deliver ‘Nurturing Care’ intervention. Each non-specialist facilitator has been assigned a case load of 8–10 mothers to deliver intervention. The fidelity of the intervention is being evaluated using an adapted ENACT tool developed for the programme. 20% of randomly selected intervention sessions from each non-specialist facilitators at different stages of the intervention delivery will be rated by the programme trainers to assess the fidelity of intervention delivery by non-specialist facilitators.

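### The primary model and the sample size treat all mothers as independent although intervention-arm mothers share up to 15 facilitators; if facilitators differ in effect, the planned standard error is somewhat too small and the power somewhat overstated

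*Protocol article*

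**What the plan says.** The Study design section describes "A two-arm, single-blinded, individual randomised controlled trial with mixed-methods process monitoring and evaluation". According to the abstract, intervention-arm mothers receive individual sessions from non-specialist facilitators. The training section states: "The programme trainers trained 15 non-specialist facilitators" and "Each non-specialist facilitator has been assigned a case load of 8–10 mothers to deliver intervention". Only those rated competent may deliver. The treatment-as-usual arm has no facilitators; both arms receive the same lady health worker visits.

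The Sample size calculations section takes "a conservative effect size of 0.4 (two-sides hypothesis) at 12 months post-partum was proposed in the present study", adds that "The effect size was calculated using the two-sided t-test", and concludes, "with 80% power, 0.05 significance and a two-sided hypothesis test and accounting for 20% attrition", that "we will need 250 caregiver–child dyads (125 in each arm"). It mentions no ICC and no design effect.

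For the primary outcome, "a linear regression model will be employed with treatment as the sole predictor". The adjusted model adds infant gender, mother's education and baseline SRQ. The only random effect named anywhere is the subject, for secondary outcomes with repeated measurements. The section refers further detail to a statistical analysis plan.

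**The concern.** This is a partially nested design: randomisation is individual, but delivery groups the intervention-arm mothers by facilitator and leaves the control mothers ungrouped. Mothers coached by the same person over more than a year may have more similar outcomes than mothers coached by different people. The article itself gives reason to expect variation. The facilitators have little or no prior experience, each is rated for competence before delivering, and fidelity is sampled from each of them. Mother–infant interaction, the primary outcome, is also what the later sessions train directly.

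If such similarity exists, 100 intervention-arm outcomes carry less information about the average effect than 100 independent ones. A regression on treatment alone then understates the variance of the intervention-arm mean. The confidence interval for the one comparison the trial is powered for becomes too narrow, and the error runs towards claiming a benefit. The t-test sample size overstates power for the same reason.

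**Working it through.** **Inputs from the article.** Standardised effect d = 0.4; two-sided significance level 0.05; power 80%; attrition 20%; 125 randomised per arm; 15 facilitators trained; caseload 8–10. The caseload fits the arm size: 15 × 8 = 120 and 15 × 10 = 150, which bracket 125.

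**Assumed, because the article does not give it.** The facilitator ICC, taken as 0.01 to 0.10. Total outcome variance is set to 1 in both arms.

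**Reproducing the stated sample size.** The t-test needs 99.08 per arm, rounded up to 100. Then 100 / 0.8 = 125 per arm, or 250 in total, as stated. Power at 100 per arm is 80.7% by normal approximation and 80.4% by the t-test. The arithmetic is right; what is in question is the independence assumption.

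**Allowing for facilitators in the intervention arm only.** With n = 100 evaluable per arm and 15 facilitators:

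- Mothers per facilitator: m = 100 / 15 = 6.67.
- Intervention-arm design effect: DE = 1 + (m − 1) × ICC.
- Correct standard error: SE = √(DE/100 + 1/100). The planned one is √(2/100) = 0.1414. Their ratio is R = √((1 + DE)/2).
- Type I error of the planned test: 2 × (1 − Φ(1.96 / R)).
- Power of a valid analysis, normal approximation: Φ(0.4/SE − 1.96).
- Satterthwaite degrees of freedom: (v₁ + v₀)² / (v₁²/14 + v₀²/99), with v₁ = DE/100 and v₀ = 1/100; power then from the noncentral t distribution.

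Worked example at ICC 0.05: DE = 1 + 5.67 × 0.05 = 1.283; R = √(2.283/2) = 1.068; SE = 0.1511; type I error = 2 × (1 − Φ(1.835)) = 6.7%; power = Φ(2.647 − 1.96) = 75.4%; degrees of freedom 40.8, giving power 73.4%.

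| Assumed ICC | DE | SE ratio R | Type I error, planned test | Power, normal | Power, Satterthwaite (df) |
|---|---|---|---|---|---|
| 0 | 1.000 | 1.000 | 5.0% | 80.7% | 79.2% (49) |
| 0.01 | 1.057 | 1.014 | 5.3% | 79.7% | 78.0% (47) |
| 0.02 | 1.113 | 1.028 | 5.7% | 78.6% | 76.8% (45) |
| 0.05 | 1.283 | 1.068 | 6.7% | 75.4% | 73.4% (41) |
| 0.10 | 1.567 | 1.133 | 8.4% | 70.4% | 68.0% (36) |

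**Sensitivity to the other inputs (normal approximation).**

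- No attrition: 125 per arm, m = 8.33. Power is 82.8% at ICC 0.05 and 77.2% at 0.10, against 88.5% under independence.
- About 10% attrition: 112 per arm. Power is 82.7% at ICC 0.02 and 79.3% at 0.05.
- Fewer facilitators delivering: at caseloads of at most 10, 125 mothers need at least 13 (125 / 10 = 12.5). With 13 and 100 evaluable, power is 74.5% at ICC 0.05 and 68.7% at 0.10.

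**The case against.** **The size rests on an assumed ICC.** This stands. At 0.01 the standard error moves by 1.4% and power by one point. One-to-one sessions remove the correlation that group sessions would add, although not the effect of sharing a facilitator.

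**A reader might infer that 80% power is out of reach at any realistic ICC.** The article does not support that. The shortfall assumes that the whole 20% attrition allowance is used; with none, power is 82.8% at ICC 0.05. The article also calls d = 0.4 conservative against 0.6–0.9 in the reference study. At d = 0.6 with 100 per arm, power is about 96% even at ICC 0.10.

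**A reader might infer that type I error is inflated regardless.** It is not. Mothers are individually randomised. If the intervention changes nobody's outcome, facilitators create no differences and the planned test holds its level. Inflation needs facilitators who truly differ while averaging to no effect, with inference reaching beyond these particular facilitators. That target is reasonable, because the Dissemination section aims at scale-up through non-specialist facilitators, but it is a choice of inference.

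**Similarity may come from geography.** The article does not say how mothers were allotted to facilitators. If caseloads follow area, part of the similarity is an area effect that control mothers share. In a simulation with area effects balanced across arms (40,000 runs, ICC 0.02–0.10), the planned test's type I error was 4.9% falling to 4.1%, so not inflated. A facilitator term in one arm could then widen the interval needlessly. This stands as a caution on the remedy.

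**The detail may sit in the analysis plan.** This stands only in part. A sensitivity analysis may be there, but the article already fixes the primary model as having a sole predictor, so this is a stated choice and not a gap.

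**Conclusion.** The concern holds conditionally. The structure is documented: up to 15 facilitators in one arm, none in the other, and independence assumed in both the primary model and the sample size. The direction follows for any positive facilitator ICC when inference is to facilitators generally.

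The size is modest and cannot be fixed from the article. Over the assumed ICC range, at full 20% attrition and with 15 facilitators, it runs from negligible to a loss of about ten points of power and a type I error above 8%. Lower attrition improves the power; fewer active facilitators worsen it. This is a point that should be fixed, not one that undermines the trial.

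**What to change.** Before analysis:

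- Prespecify that the primary comparison accounts for facilitator in the intervention arm: a partially nested mixed model with a random facilitator effect in that arm only, arm-specific residual variance, and Satterthwaite or Kenward–Roger degrees of freedom. Use the caseload assignments already held, and report the estimated ICC.
- Keep the treatment-only regression as a sensitivity analysis.
- State how mothers were allotted to facilitators. If caseloads follow geography, check whether an area effect shared by both arms explains the similarity.
- Restate power at full 20% attrition as about 68–78% for ICC 0.10–0.01 under this model, with the ICC labelled an assumption. The normal-approximation figures (70–80%) would not match a model with small-sample degrees of freedom.

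Do not enrol more participants. The cost is a few sentences in the plan and one linking variable. The downside is a slightly wider confidence interval and a slightly lower stated power.
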